### 3.2. Pathogenesis of Ebola Virus, Host immune responses and Ebola Virus Disease severity

Ebola virus enters the human host body through mucosal surfaces as well as breaks and abrasions in the skin, or by parenteral introduction. Human-human transmission during outbreaks occurs by direct contact with infected patients or cadavers. In addition, sexual transmission and ingestion of contaminated food may be possible sources of infections with Ebola virus. Immune cells of the infected host including monocytes, macrophages, and dendritic cells contribute to the dissemination of the virus from initial site of infection to regional lymph nodes, probably through the lymphatic system, and to the liver and spleen through the blood. Then the virus invades a wide range of host cells including endothelial cells, fibroblasts, hepatocytes, adrenal cortical cells, and several types of epithelial cells. All these cells provide support for intense replication to the virus. Ebola virus-induced pro-inflammatory mediators including (but not exhaustive) interleukins 2, 6, 8, and 10; interferon-inducible protein 10; monocyte chemo-attractant protein 1, (RANTES); TNF $\alpha$ ; and reactive oxygen and nitrogen may be intense and imbalanced. Dysregulated pro-inflammatory responses seem to be associated with fatal cases of EVD while timely and adequately regulated inflammatory responses seem to confer recovery. In animal model, dysregulation by inhibition of the type I interferon response may be a key

player in the pathogenesis of Ebola virus and Marburg Virus. Virus particles like VP35 function as a type I interferon antagonist by blocking activation of interferon regulatory factor and possibly by preventing transcription of interferon  $\beta$ . Similarly, expression of VP24 of the Ebola virus interferes with type I interferon signaling pathways and favors the ability of Zaire Ebola virus to induce death in mouse. These imbalanced immune responses are associated with high concentrations of nitric oxide in patients infected with Zaire Ebola virus and Sudan Ebola viruses. Abnormal production of Nitric oxide may be a negative predictor of Ebola virus induced-disorders including apoptosis of bystander lymphocytes, tissue damage, and loss of vascular integrity and in turn contribute to EVD severe manifestation like hemorrhage and shock.

### 3.3. Vaccine against Ebola Virus

Although no causal treatment and vaccine are so far available to address EVD, researchers have made significant progress over the last years. Currently, the following vaccine platforms in pre-clinical development are demonstrated to be of interest against EBOV and MARV: virus-like-particles (VLPs), Venezuelan equine encephalitis virus replicons (VEEV RP), replication incompetent adenovirus serotype 5 vectors, replication competent recombinant human parainfluenza virus 3 (rHPIV3) and recombinant vesicular stomatitis virus (rVSV). The rVSV platform is one of the most promising vaccine candidate approaches against filoviruses. The

VSV is a nonsegmented, negative-stranded RNA virus in the family Rhabdoviridae, which is an animal pathogen and does not cause serious disease in humans. Two serotypes of the VSV circulate on the American continent, serotypes New Jersey and Indiana. Livestock are the preferred host via transmission by mosquitos, sandflies or blackflies. Manifestations are vesicular lesions on the mouth and teats. Humans are rarely infected and even in the event of an infection, the disease course is generally asymptomatic or mild. Several VSV characteristics makes it a good vaccine vector: replication in mammalian cell lines, growth to very high titers, and a strong induction of innate and adaptive (humoral as well as cellular) immune responses, very low levels of pre-existing immunity to VSV in the general population. As an additional benefit, it induces neutralizing immune response primarily directed against the VSV glycoprotein (VSV-G). This characteristic is used in designing the Ebola vaccine. The VSVΔG-ZEBOV vaccine consists of a recombinant Vesicular Stomatitis Virus (VSV), in which the Ebolavirus Zaire envelope glycoprotein has been substituted to the G coat glycoprotein. Thus the final recombinant vaccine conserves all other VSV functions, but no other Ebolavirus functions except those associated with the envelope glycoprotein.

The recombinant virus can be attenuated and be manufactured at high titers. The use of attenuated rVSV as platform for vaccine against filovirus has been demonstrated to be safe in mouse and NHP. Animal vaccinated with, rVSV-ZEBOV-GP, or rVSV-MARV-GP did not experience any major toxicity including neurotoxicity which is commonly reported in groups of animals infected with the wild type of VSV. In pre-exposure pre-clinical studies in NHP, the vaccine showed 100% efficacy. Post-exposure prophylaxis allows survival of 50% of non-human primates. The VSVΔG-ZEBOV vaccine has been given to laboratory worker in conditions of post exposure and showed to be safe.

### 3.4. Rationale of current project

Ebola Virus Diseases (EVD) are historically sporadic outbreaks, which occur in remote areas of tropical forest mainly in Central Africa. Although EVD are associated to a high case fatality rate, Ebola virus transmission was so far low and outbreaks were often rapidly contained in their area of occurrence. Vaccination to prevent infection with EV-outbreaks in human may have been considered impractical due to the sporadic incidence of the EVD despite evidence that recombinant vaccines can be effective in non-human primate models. However, the outbreak, which is occurring in West Africa, has changed the paradigm and a need for vaccine for pre-exposure of health care workers and post exposure of infected patients is now urgent. In contrast to the historical outbreak, this one is associated with an intense transmission in Guinea, Liberia and Sierra Leone. This Western African outbreak EVD is now recognized as a major and global health security concern as it spreads out unprecedentedly to capital cities and across countries; Nigeria and Senegal have so far reported imported cases. The burden on the already weak health systems in the 3 most affected countries is devastating and makes the outbreak out of control. Therefore, WHO is coordinating a global Response Road Map with the goal to stop EVD transmission globally within 6 to 9 months. Among the major mean to reach this objective, prompt clinical evaluation of safety and immunogenicity of existing candidate vaccine is a top priority. The present study aims to provide clinical data on the VSVΔG-ZEBOV candidate vaccine by end of 2014.

## 4. Trial Design

### 4.1. Overview

LA-BPSC10001-01 is a Phase I, open-label, randomized, dose escalation trial. LA-BPSC10001-01 is designed to establish safety, tolerability and immunogenicity of three dose levels of VSVΔG-ZEBOV, an Ebola Virus Vaccine Candidate for the first time in sub-Saharan African populations. In LA-BPSC10001-01 trial, 201 volunteers will be randomized. The study will be conducted in Lambaréné, Gabon. There will be seven cohorts. Cohort 1 will be of participants receiving the dose  $3 \times 10^5$  pfu, cohort 2 will receive  $3 \times 10^6$  pfu of VSVΔG-ZEBOV and cohort 3  $2 \times 10^7$  pfu. Cohort 4 will be receiving the lowest dose of  $3 \times 10^3$  pfu, followed by cohort 5 which will receive  $3 \times 10^4$  pfu. Cohorts 6 and 7 will receive  $2 \times 10^7$  pfu. All doses will be administered intramuscularly. Vaccination of subjects in each cohort will proceed in a staggered fashion. Eligible adult volunteers will be randomized into the first 5 study cohorts. However, at the time of the submission of the study amendment 3, 60 eligible participants were already randomized and vaccinated in the cohort 1, 2 and 3 (20 into cohort 1, 39 into cohort 2 and one into cohort 3). Therefore, new randomization list will be generated according to the study requirements of having additional 61 vaccinees in the cohort 3, 20 in the cohort 4 and 20 in cohort 5.

On Day 1, the 1st volunteer of cohort 1 will be vaccinated, followed by the 2nd and 3rd volunteer on Day 3. If no safety concerns arise a group of 5 participants will be vaccinated on day 5. If the holding criteria have not been met and there are no safety concerns, the

next 5-10 participants will be vaccinated. Upon completion of visit 5 by the first 5-10 vaccinees of cohort 1 the DSMB' will do a review of safety data. Cohorts 2 and 3 will be run in parallel upon the go decision of DSMB after safety data review. Participants will be enrolled in Cohorts 3,4,5,6 and 7 and vaccinated in an identical manner to the Cohort 1 and 2. Children and adolescents will be enrolled and vaccinated into cohort 6 and 7 respectively only after the first 10 participants vaccinated in cohort 3 have reach D 28 follow-up. Following the first 10 participants, volunteers will be vaccinated in groups of 5-10 per day irrespective of the cohort. Vaccinees will be observed 30 min to one hour after vaccination and occurrence of any reaction will be carefully monitored.

For each volunteer, there will be a 180-day period of active follow-up after vaccination. An additional 180 days of passive follow-up may take place upon a study amendment. Overall this study will be completed in a period of maximum 18 months. The primary endpoint will be reached for all study participants within 2 to 3 months.

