|               | 
populations living in Lambaréné, Gabon. One hundred and sixty one adult volunteers will be randomized into five dosage groups, and a further 40 school aged and adolescent volunteers will be vaccinated with a <math>2 \times 10^7</math> pfu dose.. There will be seven cohorts. Vaccination of subjects in each cohort will proceed in a staggered manner (1 to 10 participants per day will be vaccinated with a waiting time of 1 hour for each participant after vaccination). This study is part of the VEBCON consortium that is aiming to generate harmonized data for this vaccine candidate to allow optimized rapid decisions on dosage, safety, and immunogenicity as well as regulatory approval. The VEBCON consortium includes partners from Africa, EU, WHO. Partner from USA may join VEBCON or work closely. There will be in parallel to this study, similar Phase I trials in USA, Switzerland, Germany and Kenya.
 
VSVΔG-ZEBOV dose selection
 
So far, VSVΔG-ZEBOV vaccine was given to one German laboratory worker at <math>5 \times 10^7</math> pfu dosage in Ebola virus post exposure conditions. S/he experienced transient fever and very low-level VSV viremia for 2 days. Doses selected to be tested in this trial are: <math>3 \times 10^3</math> pfu, <math>3 \times 10^4</math> pfu, <math>3 \times 10^5</math> pfu, <math>3 \times 10^6</math> pfu, <math>2 \times 10^7</math> pfu in Gabon. The reference dosage of <math>5 \times 10^7</math> has been administered in post-exposure conditions. Lower doses therefore may be immunogenic enough, better tolerated and safer for pre-exposure purposes. Thus within the VEBCON consortium and in US, a large range of doses: <math>10^3</math> to <math>10^8</math> will be tested to support as best as possible discussion on appropriate dosage for pre-exposure and potentially post exposure purposes..
 |

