##### **Holding Rules**

Participants will be followed a minimum of 60 minutes after vaccination. As such, immediate hypersensitivity reaction (in the 60 minutes following vaccination) will be assessed. All vaccinees will be monitored the day after injection in case of cytokine storm (in the 24 hours following vaccination). If any of the subjects has a vaccine related SAE, vaccinations will be held for the remainder of the study participants until a decision on vaccination resumption is reached. Vaccinations will resume upon agreement of the DSMB, the PI, the sponsor and VEBCON partner.

The following holding rules apply to each cohort of subjects. Solicited and unsolicited AEs and safety laboratory data will be recorded and tracked by the PI after immunization. The research monitor will review the AEs (local, clinical systemic, and laboratory systemic). If any holding rules are met, no further vaccination will be administered in any cohort until the investigators have conferred with the safety monitor and a full written report has been submitted to the Sponsor, the CERMEL SRC, the CERMEL IRB and the Gabonese NEC.

- One or more participants experience any SAE related to the study product (possible, probable or related), or
  - A suspected unexpected serious adverse drug reaction (SUSAR) occurs that is life-threatening or results in death.
- If any other observation occurs that in the opinion of the PI results in a recommendation to halt enrollment

After an holding rule is activated, a thorough review by the PI, safety monitor, and DSMB will occur. Vaccination of the subjects may resume only if the DSMB, the PI, and the sponsor agree it is safe to resume vaccinations and the following considerations are discussed.

- Relationship of the AE or SAE to the vaccine

- Relationship of the AE or SAE to the vaccine dose (eg, only associated with high dose group)
- If appropriate, additional screening or laboratory testing is provided to other subjects to identify subjects who may develop similar symptoms
- If any study related SAE is not listed on the current informed consent form (ICF), the PI will revise the ICF and volunteers will be asked to provide consent on the new ICF

The VEBCON partners will be notified if a holding rule is activated or released. If the clinical trial is halted and is unable to resume, a formal letter will be sent to the country specific regulatory authorities by the sponsor explaining the reasons for cessation of the study.

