### Administration of study vaccines:

Serious allergic reactions including anaphylaxis may occur and for this reason volunteers will be inoculated in a clinical area where Advanced Life Support trained physicians, equipment and drugs are immediately available for the management of any serious adverse reactions. Participants will be observed for one hour after vaccination.

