### **6.3. Study Enrollment/ vaccination (Visit 2, Day 0)**

Vaccination with BPSC1001 will occur at Visit 2. Potential participants will be listed upon information sessions and their willingness to participate. They will be then screened by block of 5-10 volunteers after informed consent signature. Eligible participants will be given a study identification number which for adults will be used for random selection to one of 5 cohorts. The randomization will be done using a software. The randomization will be detailed in a study procedure.

Subjects will have only one vaccination visit during the course of the study. Each subject will receive an injection of BPSC1001 into the outer aspect of the subject's upper arm (deltoid area). The following procedures will be performed during each injection visit:

- Review of subject's medical history (including concomitant medications) since previous visit

- Check of inclusion / exclusion criteria
- Directed physical examination (proposed injection site) and vital signs check
- Urine sample collection for determination of:  
Urine pregnancy test (females only)\*
- Injection with study product
- Post-injection observation period of at least 60 min.
- Study visits schedule , thermometer ( for axillary temperature), and ruler distribution and review of use
- Provision of emergency contact card
- Repeat examination of injection site and vital signs check
- Review of any immediate AE

\*All female subjects of childbearing potential will be required to submit a urine sample for onsite pregnancy testing on the day of injection, and the test results must be negative prior to administration of the vaccine.

#### 6.4. Follow-Up Visits: visit 3 to visit 10

There will be 8 follow-up visits (Visits 3 through 10). Table 3 outlines visits, study days, and visit windows. The following procedures will be performed during each follow-up visit:

- Review of subject's medical history (including concomitant medications and AE) since previous visit
- Directed physical examination and vital signs check
- Review solicited symptoms (4 visits; Visits 3, 4, 5, 6, )
- Collection of approximately 6 to 92 mL whole venous blood for the determination of:
  - WBC
  - Serum chemistry profiles (Creatinin, AST, ALT) will be performed only at visits 5,7,9,10.
  - Blood for immunological analyses
  - Blood for virus isolation
- Urine and saliva for virus isolation

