The CERMEL has two building facilities for clinical activities. The smallest is dedicated for early phase trials including Phase I/II studies. There are distinct areas in the phase I/II facility: an intervention area where vaccine administration will take place. In the post vaccine surveillance area, there 3 beds, life support equipment and drugs available for any major safety issue. In addition, CERMEL works closely with the two tertiary hospitals where hospitalization in mid or long term will take place. The main laboratory building hosts the department of hematology/biochemistry (called clinical laboratory) and the immunology and the molecular biology sub-units (together called research laboratory). The research laboratory hosts two more sub-units: the tuberculosis laboratory and the helminthes research laboratory (or parasitological laboratory). Staff 'offices, meeting and conference rooms as well as the basement and the cold chain management area are located in the administrative building facility. CERMEL has an automobile park comprising of 5 cars including one bus. There is well functioning mobile phone coverage in Gabon, for national and international calls and communication.

There are IATA certified staff available to handle technical and logistic issues related to shipment and importation of vaccines. Import license for research goods has to be obtained at the drug office of the Ministry of Health in Libreville. IT, data entry and data analysis services are supported by VSAT internet connection via satellite, enabling efficient real time data entry and statistical support for clinical trials.

Health care services currently available to provide care for children with influenza and other respiratory illnesses

The health care infrastructure consists of two main hospitals, the Albert Schweitzer Hospital and the Lambaréné Regional Hospital (HRL). The HRL is situated near the airport of Lambaréné with a driving distance of about 15 km between HAS and HRL. In both hospitals, there are a pediatric ward, surgery, internal medicine, antenatal clinics and emergency services which can admit patients 24 hours per day as well as X-ray departments. In addition to these two hospitals, there are two primary health centers (Makouké and Fougamou) and about 10 functioning dispensaries in the villages and along the river Ogooué. The primary health centers and the dispensaries provide treatment for fever management.

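### Section 4.1 allows observation to end at 30 minutes, against the 60-minute minimum in Sections 4.6 and 6.3

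*Protocol*

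**What the plan says.** The protocol states the post-vaccination observation time in five places.

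- **Section 4.1, Overview:** "Vaccinees will be observed 30 min to one hour after vaccination".
- **Section 4.6, Holding Rules:** "Participants will be followed a minimum of 60 minutes after vaccination". The next sentence gives the purpose: "immediate hypersensitivity reaction (in the 60 minutes following vaccination) will be assessed".
- **Section 5.7, Administration of study vaccines:** "Participants will be observed for one hour after vaccination".
- **Section 6.3, Visit 2 procedures:** "Post-injection observation period of at least 60 min".
- **Synopsis, Study design:** vaccination is staggered "with a waiting time of 1 hour for each participant after vaccination".

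Two further statements concern the setting. Section 5.7 notes that anaphylaxis may occur and therefore requires that "volunteers will be inoculated in a clinical area where Advanced Life Support trained physicians, equipment and drugs are immediately available". Annex 1, describing the Phase I/II facility, says: "In the post vaccine surveillance area, there 3 beds, life support equipment and drugs available for any major safety issue".

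**The concern.** The choice of 60 minutes is not in dispute. The protocol set that figure itself and tied it to a named hazard. The difficulty is that Section 4.1, which describes how vaccination proceeds (staggering, review by the monitoring board, daily group sizes), gives a range whose lower end is half the minimum stated elsewhere.

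What is at stake is participant safety. Someone released at 30 minutes under Section 4.1 could be away from the staff, equipment and drugs described in Section 5.7 and Annex 1 during the second half of the hypersensitivity window. Vaccination was continuing at 2 × 10^7 pfu in adults, and cohorts 6 and 7 take the same dose to adolescents and to children from age 6.

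There is also a smaller compliance question. A release at, say, 35 minutes would comply with Section 4.1 and deviate from Sections 4.6 and 6.3, so it is unclear whether it should be recorded as a protocol deviation.

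**Working it through.** This is a comparison of statements. The plan reports no figure on this point to reproduce.

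**Statements side by side**

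| Place | Shortest stay allowed | Form of the statement |
|---|---|---|
| Section 4.1 | 30 min | range, 30 to 60 min |
| Section 4.6 | 60 min | minimum |
| Section 5.7 | 60 min | fixed, one hour |
| Section 6.3 | 60 min | minimum |
| Synopsis | 60 min | waiting time, one hour |

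The upper end of the Section 4.1 range only equals the floor in Sections 4.6 and 6.3. Every stay from 30 minutes up to, but not including, 60 minutes is allowed by Section 4.1 and excluded by the other two. No section limits the 30-minute bound to a particular cohort, age group or dose. Section 4.1 is current text: it reports the position at submission of Amendment 3.

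**Shortfall per participant**

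- Window to be covered (Section 4.6): 60 min.
- Shortest stay under Section 4.1: 30 min.
- Largest gap: 60 − 30 = 30 min, and 30 / 60 = 50% of the window.

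**How many participants the wording could still affect**

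- Total planned (Synopsis, Section 4.1): 201.
- Already vaccinated at Amendment 3 (Section 4.1): 20 + 39 + 1 = 60.
- Remaining: 201 − 60 = 141.
- Check by cohort: 61 + 20 + 20 = 101 adults in cohorts 3, 4 and 5; 20 + 20 = 40 minors in cohorts 6 and 7; 101 + 40 = 141.

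**Ceiling**

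141 × 0.5 h = 70.5 participant-hours without direct observation. This would require every remaining participant to be released at exactly 30 minutes.

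**After the change**

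With a 60-minute minimum in Section 4.1, the gap is 60 − 60 = 0 min.

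**The case against.** The strongest reply is that the operative instructions are already right. Section 4.1 is an overview. Staff on vaccination day work from Section 6.3, which requires at least 60 minutes and then a repeat injection-site examination, a vital-signs check and a review of immediate events. Section 4.6 also states a minimum. A stay of exactly 60 minutes satisfies every section, and Section 4.1 does not direct anyone to release a participant at 30 minutes. For harm to follow, staff would have to prefer the overview to the procedure list, and a reaction would have to begin between 30 and 60 minutes. The protocol gives no rate for such reactions.

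Most of this stands as a limit on the practical risk:

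- The participant-hours figure measures neither risk nor likelihood.
- The Synopsis is weaker support, because its waiting time appears in a description of staggering and may refer to pacing. The point does not depend on it.
- The loss of life-support cover is an inference: neither Section 5.7 nor Annex 1 says where a participant released early would be.

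It does not remove the contradiction. That a 60-minute stay complies everywhere does not help when Section 4.1 also authorises shorter stays that two other sections forbid.

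**Conclusion.** The concern holds. Section 4.1 contradicts Sections 4.6 and 6.3, and also the one hour in Section 5.7, on a participant-safety rule. The supported size is a gap of up to 30 minutes per participant, half of the protocol's own hypersensitivity window. The ceiling for the 141 participants still to be vaccinated is 70.5 participant-hours.

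The consequence is conditional on staff following Section 4.1 rather than the Section 6.3 list, and the document does not show how often that would happen. No effect on the safety data or the holding rule is claimed. Later reactions would still be picked up at the Day 1 visit and through the memory aid or diary, and a vaccine-related serious adverse event triggers the hold whenever it occurs. This is an internal inconsistency that should be corrected; it is not a flaw in the observation time the sponsor intended.

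**What to change.** In Section 4.1, replace the range of 30 minutes to one hour with a requirement of at least 60 minutes, matching Sections 4.6 and 6.3. No other section needs to change.

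The cost is one phrase in a protocol amendment. It adds no work for staff already following the Section 6.3 procedures.
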